## Abstract

**Introduction:**

Globally, tuberculosis (TB) is a leading cause of death in women of reproductive age and there is high risk of reactivation of latent tuberculosis infection (LTBI) in pregnancy. The uptake of routine screening of migrants for LTBI in the UK in primary care is low. Antenatal care is a novel setting which could improve uptake and can lend insight into the feasibility and acceptability of offering opt-out screening for LTBI.

**Methods and analysis:**

This is an observational feasibility study with a nested qualitative component. The setting will be the antenatal clinics in three hospitals in East London, UK. Inclusion criteria are pregnant migrant women aged 16–35 years attending antenatal clinics who are from countries with a TB incidence of greater than 150/100 000 including sub-Saharan Africa, and who have been in the UK for less than 5 years. Participants will be offered LTBI screening with an opt-out interferon gamma release assay blood test, and be invited to complete a questionnaire. Both participants and healthcare providers will be invited to participate in semistructured interviews or focus groups to evaluate understanding, feasibility and acceptability of routine opt-out LTBI screening. The primary analysis will focus on estimating the uptake of the screening programme along with the corresponding 95% CI. Secondary analysis will focus on estimating the test positivity. Qualitative analysis will evaluate the acceptability of offering routine opt-out LTBI screening to participants and healthcare providers.

**Ethics and dissemination:**

The study has received the following approvals: Health Research Authority (IRAS 247388) and National Health Service Ethics Committee (19/LO/0557). The results will be made available locally to antenatal clinics and primary care physicians, nationally to NHS England and Public Health England and internationally through conferences and journals.

**Trial registration number:**

NCT04098341.

Strengths and limitations of this studyThe study uses a novel approach of tackling a complex problem of low uptake of latent tuberculosis infection (LTBI) screening in migrants by using an opt-out method and a novel setting: antenatal care.The study creates new education and training tools for healthcare professionals working in antenatal care.Our findings will provide a greater understanding of the acceptability of LTBI screening among pregnant migrant women and healthcare professionals.As this is an observational study, we are unable to demonstrate causality from our results.Not being able to interview women who decline LTBI screening may reduce the validity of our findings.

## Introduction

### Context

Tuberculosis (TB) remains a significant global health problem affecting an estimated 10 million people worldwide in 2019 leading to 1.4 million deaths.^1^ TB is one of the leading causes of death in women of reproductive age (15–45 years).^2^ In 2018, an estimated 3.2 million women globally were infected with TB and almost half a million women died from TB.^3^ Indirect maternal deaths account for 28% of total maternal deaths, of which 15%–35% are due to TB.^2^

The WHO defines latent tuberculosis infection (LTBI) as a ‘state of persistent immune response stimulation by *Mycobacterium Tuberculosis* antigens without evidence of clinically manifested active TB’.^1^ A quarter of the world’s population is estimated to have LTBI.^4^ Individuals with LTBI have no signs and symptoms of active TB but remain at risk of developing active TB in their lifetime. LTBI acts as a reservoir for active TB and TB elimination requires strategies for LTBI control.^5^ The risk of reactivation of LTBI is higher in pregnancy.^6^ This risk may be due to T-cell suppression and reduced interferon-gamma production.^7^

In low TB incidence countries, TB transmission is limited and most active cases of TB occur due to reactivation of LTBI imported from high incidence settings.^8^ Uptake of LTBI screening in primary care is low.^9 10^ Antenatal care is a new setting for LTBI screening and understanding the factors affecting the feasibility and acceptability of LTBI screening in this setting are first steps towards developing effective interventions to improving LTBI screening uptake.

### Current knowledge

In women of childbearing age (16–45 years), TB is one of three leading causes of death globally.^4^ Diagnosis of TB in pregnancy is often delayed as pregnancy can mask some of the clinical manifestations of TB.^11 12^ TB in pregnancy is associated with poor perinatal, foetal and maternal outcomes.^13 14^

The UK has one of the highest TB incidence rates in Western Europe. The incidence of TB among those born outside the UK is 14 times higher at 39.0 per 100 000 population and accounting for 74% of all new cases of TB in England in 2019.^15^ Public Health England’s TB migrant health guide strategy recommends migrant screening for LTBI in high incidence areas in England such as the London Boroughs of Tower Hamlets, Newham and Waltham Forrest.^16 17^

The London Borough of Newham was spearheading a large-scale LTBI screening programme in anticipation of the national programme. A total of 20 905 LTBI tests were reported between July 2014 and June 2017 across England with nearly half of the tests taking place in Newham.^9 10^ Between April 2015 and June 2016, 5622 eligible migrants in England were offered an LTBI test, 2904 (51%) of whom attended for the test.^9^

Effective screening for LTBI is key to reducing TB incidence in the UK. There is good evidence that screening and treatment of LTBI is a cost-effective intervention that significantly reduces the risk of developing active disease and the risk of onward transmission.^18 19^ The national LTBI migrant screening programme has been rolled out but there is insufficient evidence on the best setting for uptake of LTBI screening.

There is limited qualitative research about the acceptability to women of LTBI screening in pregnancy. Reasons for low uptake may be due to stigma of having active TB or fear of a positive test result affecting their immigration status. An opt-out approach to LTBI screening may normalise the process and has the potential to reduce barriers such as stigma, as well as practical barriers.^20^

Provider knowledge and understanding of the risks of TB, screening and treatment can be a major predictor of successful management of TB.^21^ Data from a local LTBI screening programme have highlighted that offer of screening varies among general practitioner (GP) practices indicating that healthcare provider knowledge and attitude may influence offer of screening.^22^

Evaluating the impact of healthcare provider training to improve TB management has mainly been performed in low-income countries and there are only a few rigorous TB training evaluation studies available.^21^ E-learning modules use pretraining and post-training tests to evaluate acquired knowledge. A GP E-learning module has been developed by the national TB charity ‘TB Alert’ to enhance knowledge of GPs responsible for screening and treatment of LTBI but the effectiveness of the module has not been formally evaluated.

### Rationale for LTBI screening in antenatal care

Pregnancy can predispose to reactivation of LTBI and diagnosis can be delayed due to reduced awareness among healthcare providers and reluctance to investigate non-specific TB symptoms by chest radiography.^23^ Risks of LTBI reactivation and delays in diagnosis of TB can be mitigated by screening an at-risk pregnant migrant population for LTBI. A simple clinical algorithm recommended by the WHO based on the absence of current cough, fever, weight loss and night sweats can help to exclude active TB disease. Moreover, healthcare professionals will have a higher index of suspicion for active TB in interferon gamma release assay (IGRA) positive pregnant migrant women presenting with symptoms suggestive of TB, thus preventing a delay in diagnosis.^24^

Pregnant migrants may not be accessing routine healthcare and often do not have a GP. Antenatal care may therefore be a key opportunity to assess the woman’s health and screen for TB. Antenatal care provides an opportunity for health promotion such as advocating GP registration and is a time when parents may be particularly receptive to public health information and promotion.

Routine opt-out testing has proven effective for other diseases (HIV/Hepatitis B, C).^25^ Factors affecting successful uptake of screening programmes include how the test is offered, by whom, to whom and in what setting.^26^ Pregnant women screened for HIV during pregnancy perceived routine opt-out HIV testing as beneficial for both women and their unborn babies.^26^ Globally, some countries offer routine screening for TB in pregnancy mainly through symptom screen and sputum examination.^19^

LTBI screening for migrants from high TB incidence countries in antenatal care has shown high uptake in the USA, but feasibility of LTBI screening in antenatal clinics in the UK has not been evaluated.^27^

### Research hypothesis and aims

We hypothesise that offering routine opt-out LTBI screening to an at-risk pregnant migrant population in antenatal care will be feasible and acceptable to pregnant migrant women and healthcare providers.

To test our hypothesis, we will assess the uptake, feasibility and acceptability of screening an at-risk pregnant migrant population for LTBI at routine antenatal booking visits in secondary care, using opt-out IGRA testing. The results from this feasibility study will allow us to develop a definitive large-scale cluster randomised controlled trial (RCT) evaluating the effectiveness of an LTBI screening in antenatal care, the effectiveness of interventions used to maximise migrant screening for LTBI in pregnancy and to increase uptake of LTBI treatment postpartum.

## Methods and analysis

### Study protocol

This is a prospective observational feasibility study with nested qualitative research which will take place in antenatal booking clinics of three hospitals in East London (The Royal London Hospital, Newham University Hospital and Whipps Cross University Hospital). The study started on 29 April 2019 and the first participant was recruited on 3 July 2019. The study is due to finish on 31 May 2022.

Educational and training tools will be developed before the study begins. Healthcare providers involved in antenatal care will be asked to complete an E-learning module on active TB/LTBI, which has been developed by the study team, along with the national TB charity (TB Alert) and the Royal College of Midwives.

Study participants will enter the cohort when they attend the antenatal clinic for their booking appointment, after they meet inclusion criteria (table 1). Midwives will counsel and offer LTBI screening as an opt-out IGRA blood test alongside other routine investigations for blood-borne viruses at the initial booking appointment. The study will assume valid implied consent for participation if women undertake an IGRA test at the time it is offered by the midwife on an opt-out basis. Participants will be given a Participant Information Sheet by the midwife at this appointment detailing the study. Routine blood tests, including IGRA, will be taken by phlebotomists based in antenatal care.

**Table 1 T1:** Inclusion and exclusion criteria

Inclusion criteria	Exclusion criteria
Pregnant migrant women aged 16–35 years AND from high TB incidence countries (incidence of TB of >150/100 000 including sub-Saharan Africa) AND who have been in the UK for less than 5 years	Previous history of TB or LTBI Individuals who are unable to consent Evidence of current active TB (based of history, examination, blood tests, chest X-ray findings or other radiological findings)

LTBI, latent tuberculosis infection; TB, tuberculosis.

At the time of offer of LTBI screening, we will record routine clinical data of all eligible pregnant migrant women including those who do not accept screening. Data on age, ethnicity, year of entry to the UK, pre-existing medical conditions and antenatal history which is routinely recorded in the medical notes will be collected.

All eligible pregnant migrant women will be screened for active TB by their midwives using a standardised symptom assessment questionnaire that includes the WHO recommended TB symptoms screen during their initial booking appointment. Study participants with a positive IGRA blood test will then undergo screening for active TB using the WHO recommended TB symptoms screen at 20 weeks, 30–34 weeks, delivery and postpartum. Data on symptoms of active TB will be collected at each time point (figure 1).

**Figure 1 F1:**
[figure not shown]
Timeline of study project (assessment and follow-up of migrant women). IGRA, interferon gamma release assay; LTBI, latent tuberculosis infection; TB, tuberculosis.

Participants will leave the study 6 weeks postdelivery or at the time of miscarriage if they have had a miscarriage.

Study participants with a positive IGRA blood test will be referred to the local TB clinic (if screened at The Royal London Hospital or Whipps Cross University Hospital) or to their GP (if screened in Newham University Hospital). TB clinics or GPs will review these individuals and initiate LTBI treatment according to local protocols.

All eligible pregnant women will be asked to complete a short questionnaire on acceptability of LTBI screening, knowledge about TB/LTBI and barriers to screening. At the end of pregnancy, women will be asked to complete the same questionnaire to compare the perception and knowledge of active TB/LTBI before and after the screening intervention. Trained research personnel will obtain written informed consent from the participant for the questionnaire.

We have used the Standard Protocol Items: Recommendations for Interventional Trials reporting guidelines for this paper.^28^

### Outcomes

Our primary outcomes are (i) the uptake of screening for LTBI in antenatal care assessed by the proportion of eligible migrant women offered a test who accepted LTBI screening, and (ii) the offer of IGRA blood test screening by healthcare providers assessed by the proportion of migrant women eligible for screening who were offered an IGRA test.

Secondary outcomes are as follows: rates of LTBI and active TB identified in pregnant migrant women during the study period, time to diagnosis, understanding and acceptability of LTBI screening and acceptability of interventions to increase screening uptake, perceived facilitators and barriers influencing uptake of LTBI screening and treatment uptake postpartum, increase in knowledge and awareness about active TB/LTBI among pregnant migrant women and healthcare providers and estimation of some of the parameters required for evaluation of cost-effectiveness of LTBI screening in antenatal care compared with primary care.

Process outcomes of the study are the numbers of eligible participants and screening acceptance rate, proportion of eligible pregnant migrant women who were offered LTBI screening, views and experiences of participants on study recruitment methods, data collection methods and retention in the study and level of NHS support required for the proposed definitive cluster RCT.

### Patient and public Involvement

Healthwatch Newham conducted a survey to evaluate patient experiences of the LTBI screening programme in Newham, to identify the key factors that influence the uptake of screening, and to understand why patients decline screening. The results of this survey have influenced the design of this study, and migrants with LTBI have provided useful information about how LTBI screening could be better conducted. Evaluation of patient experiences demonstrated that migrants would like to be offered a LTBI test directly by their GP or nurse and that the test should be part of a general check-up. Our intervention has been designed to provide this by incorporating the offer of an IGRA test into routine antenatal care check-ups by midwives. The concept and the study design has been developed in close collaboration with TB Alert (UK TB charity), with the support of the East London Katherine Twining network PPI group (Katie’s Team) and the Centre for Maternal and Child Health Research at City, University of London’s service user panel and former TB/LTBI patients. PPI members felt that testing for LTBI as an opt-out approach is an acceptable intervention for pregnant migrant women.

### Sample size

A sample of 200 pregnant migrant women offered testing allows this study to estimate the screening uptake rate (key primary outcome for the feasibility study) with adequate precision across a range of possible values of the rate. If the uptake rate is 50% (at which precision is lowest), then this can be estimated within 6% either side, that is, a 95% CI of 44%–56%. If, however the rate is as high as 80% (or equivalently as low as 20%), then the rate can be estimated within 5%.

These precision calculations are based on the standard normal approximation and formula for a 95% CI for a proportion p based on a sample size n: p±1.96 x sqrt[px(1-p)/n].

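### With 200 women, the protocol's own formula gives a 95% CI of ±6.9 points at 50% uptake and ±5.5 points at 80%, not the stated ±6 and ±5.

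*Protocol article*

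**What the plan says.** The Sample size section of the protocol article sets the number and its purpose: "A sample of 200 pregnant migrant women offered testing allows this study to estimate the screening uptake rate". It then gives two precision statements. At 50% uptake, "this can be estimated within 6% either side, that is, a 95% CI of 44%–56"%. For more extreme rates, "If, however the rate is as high as 80% (or equivalently as low as 20%), then the rate can be estimated within 5"%. The section names its method: "These precision calculations are based on the standard normal approximation and formula for a 95% CI for a proportion p", followed by the expression "p±1.96 x sqrt[px(1-p)/n"].

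The Outcomes section defines uptake as "the proportion of eligible migrant women offered a test who accepted LTBI screening", so the 200 women offered testing are the denominator of the proportion. The Statistical analysis section makes estimation of uptake with its 95% CI the primary analysis. The article gives no other sample size, confidence level or population-size correction for this calculation.

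**The concern.** One short section fixes the sample size, the confidence level, the formula and the results. The results do not come out of the other three, and both stated margins are narrower than the formula allows.

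No hypothesis test, and so no power calculation, is planned for uptake. Precision is therefore the whole design criterion, and the claim that 200 women are enough rests on these two figures. The 50% case is also realistic: the Current knowledge section reports that 2904 of 5622 migrants offered a test in England attended for it, about half. A reader judging whether the study is large enough, or using it as a template when sizing later work, is given a more favourable picture than the design delivers.

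**Working it through.** **Inputs, all from the Sample size section**

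- n = 200 women offered testing
- two-sided 95% confidence, multiplier 1.96
- half-width h = 1.96 × √(p(1 − p)/n)
- scenarios p = 0.50, and p = 0.80 or 0.20
- stated results: h = 6 points (44% to 56%) and h = 5 points

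**Attempt to reproduce the stated figures**

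- p = 0.50: h = 1.96 × √(0.25/200) = 0.0693. The interval is 43.1% to 56.9%, a full width of 13.9 points against the stated 12.
- p = 0.80: h = 1.96 × √(0.16/200) = 0.0554. The interval is 74.5% to 85.5%.
- p = 0.20: the same half-width, with interval 14.5% to 25.5%.

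Neither stated figure is reproduced.

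| Uptake | Stated half-width | From the formula, n = 200 | Ratio |
|---|---|---|---|
| 50% | 6 points | 6.93 points | 6.93/6 = 1.15 |
| 80% or 20% | 5 points | 5.54 points | 5.54/5 = 1.11 |

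**Sample size needed for the stated half-widths**, from n = 1.96² × p(1 − p)/h²

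- ±6 points at 50%: 3.8416 × 0.25/0.0036 = 266.8, so 267 women
- ±5 points at 80%: 3.8416 × 0.16/0.0025 = 245.9, so 246 women

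**Could something else explain the figures?**

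- *Rounding.* 6.93 and 5.54 round to 7 and 6. To round down to 6 and 5, the half-widths would have to be below 6.5 and 5.5 points. That needs n above 3.8416 × 0.25/0.065² = 227.3 and above 3.8416 × 0.16/0.055² = 203.2.
- *Another 95% interval at n = 200.* At 50% uptake, Wilson, Agresti-Coull and Jeffreys each give 43.1% to 56.9%, Clopper-Pearson gives 42.9% to 57.1%, and the continuity-corrected normal interval gives ±7.2 points. All are wider than 44% to 56%. At 80% the half-widths of these alternatives run from 5.5 to 5.8 points.
- *A lower confidence level.* Taken literally, ±6 and ±5 points at n = 200 imply multipliers of 0.06/√(0.25/200) = 1.70 and 0.05/√(0.16/200) = 1.77, or about 91% and 92% confidence. A 90% multiplier of 1.645 gives 5.8 and 4.7 points, which round to the stated values.
- *A larger sample.* n = 250 gives 6.2 and 5.0 points, which also round to the stated values.
- *A finite-population correction.* The two figures would need different population sizes, about 796 and 1068. The article gives none.

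A 90% level or a sample of about 250 would match after rounding, but the article states neither. Where the figures came from is conjecture, and the finding does not depend on it.

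**The case against.** The strongest reply is about consequence, since the arithmetic itself cannot be defended. This is a feasibility study that claims only adequate precision. It ties no maximum width, progression rule or power requirement to 6 points. The discrepancy is 0.93 points at 50% and 0.54 points at 80%. The final interval will be computed from the observed data, so the planning error does not carry into the reported uptake, and planners of the later cluster trial can use that interval.

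Most of this stands. The harm is to the justification of the sample size as presented to readers of the protocol; the eventual estimate is unaffected. It does not excuse the figures, because the section prints its formula and writes out an explicit interval, and both are offered as the reason why 200 is enough.

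A second reply is that the article does not show which element is wrong: the half-widths could be the real target and the sample size the slip. That is fair. But 200 is the only sample size given, and the section presents the half-widths as consequences of it, so correcting the half-widths is the natural reading.

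Nor does the fact that an article condenses a longer protocol help. Nothing is left out here; the calculation is printed and its result is incorrect.

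**Conclusion.** The stated precision is wrong as written. Under the section's own formula, with 200 women offered testing and 95% confidence, the half-width is 6.93 points at 50% uptake and 5.54 points at 80% or 20%. The stated 6 and 5 understate the uncertainty: the true half-widths are 15% and 11% larger. The conclusion assumes only what the section states: n = 200 as the denominator of uptake, a two-sided 95% interval and simple binomial variation.

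It needs correcting because it is the sole quantitative basis for the sample size of the main outcome. The practical effect is modest: 200 women still estimate uptake to within about 7 points at worst, and nothing in the article shows that this would be unacceptable.

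**What to change.** Keep 200 women and replace the two precision statements with:

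- at 50% uptake, ±6.9 percentage points (95% CI 43.1% to 56.9%);
- at 80% uptake, ±5.5 points (74.5% to 85.5%), and at 20%, ±5.5 points (14.5% to 25.5%).

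The cost is two corrected sentences and a slightly less favourable precision claim, with no change to participants, procedures or analysis. If the sponsor does regard ±6 points at 50% as a requirement, the sample size must change instead, to 267. That is 67 more women offered testing (67/200 = 34% more). It would also cover ±5 points at 80%, which needs 246.

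An optional improvement is to report the final intervals by the Wilson method. The article names the normal-approximation formula only for planning, so this is not an error in the analysis plan. It would matter if uptake or the offer rate came out close to 100%, which is plausible for an opt-out test: at n = 200 the exact coverage of the normal-approximation interval is about 92.6% for a true rate of 95%, and 86.5% for a true rate of 99%. At 50% and 80% its coverage is about 94%, so the method makes little difference there.

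### The planned precision and association tests treat women as independent although midwives make the offer, so the precision for uptake is optimistic by an unknown, possibly small, amount

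*Protocol article*

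**What the plan says.** The Sample size section of the protocol article says: "A sample of 200 pregnant migrant women offered testing allows this study to estimate the screening uptake rate". It gives precision of 6 points either side at 50% uptake (an interval of 44% to 56%) and 5 points at 80% or 20%. On the method it says: "These precision calculations are based on the standard normal approximation and formula for a 95% CI for a proportion p". The formula contains only p and n. There is no design effect and no remark on clustering.

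The Statistical analysis section plans a 95% CI for uptake, χ² tests with odds ratios, and multiple logistic regression. It mentions neither midwife nor hospital and does not name the CI method.

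The design runs in "antenatal booking clinics of three hospitals in East London", with midwives counselling women and making the offer (Study protocol). On provider influence, Current knowledge reports from a local programme that "offer of screening varies among general practitioner (GP) practices indicating that healthcare provider knowledge and attitude may influence offer of screening". The rationale section adds that uptake of screening programmes depends, among other things, on who offers the test, how, and in what setting. The primary outcomes are uptake among women offered a test, and offer among eligible women (Outcomes).

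**The concern.** A simple binomial interval is valid when women's responses are independent. Here each midwife is likely to counsel several women, and offering the test is itself an act of the midwife. If midwives differ in how, or how consistently, they present the test, women seen by the same midwife resemble one another, and 200 women carry less information than 200 independent ones. The χ² test and logistic regression in their standard form rest on the same assumption.

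At stake is how far the uptake estimate can be trusted when it is carried into the planning of the cluster randomised trial. An interval that ignores positive clustering looks tighter than it is. The midwife is also not among the data items that the Study protocol section lists for eligible women. If that identity is not captured, clustering cannot be examined afterwards.

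**Working it through.** **Inputs from the article.** n = 200 women offered testing; 95% confidence with z = 1.96; planning rates 50% and 80% (or 20%); three hospitals; offer made by midwives. The article gives no number of midwives, no caseload and no ICC.

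**Step 1: reproduce the stated precision under independence.** Half-width = 1.96 × √[p(1−p)/n].
- p = 0.5: 1.96 × √(0.25/200) = 0.0693, that is 6.9 points (43.1% to 56.9%). The article states 6 (44% to 56%).
- p = 0.8 or 0.2: 1.96 × √(0.16/200) = 0.0554, that is 5.5 points. The article states 5.

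The stated figures do not follow from the article's own formula with n = 200. Half-widths of 6 and 5 points would need 1.96² × 0.25/0.06² = 266.8, so 267 women, and 1.96² × 0.16/0.05² = 245.9, so 246 women. With z = 1.645 (a 90% interval) the half-widths are 5.8 and 4.7, which round to the stated values. Whether that is their origin is not stated. Any allowance for clustering has to start from 6.9 and 5.5.

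**Step 2: allow for clustering by midwife.** Cluster size m and ICC are assumptions, shown as a range.
- Design effect DE = 1 + (m − 1) × ICC
- Half-width = independent half-width × √DE
- Effective n = 200/DE
- Coverage of an unadjusted nominal 95% interval = 2Φ(1.96/√DE) − 1

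| Women per midwife (midwives) | ICC | DE | Half-width at 50% | Half-width at 80% | Effective n | Coverage if unadjusted |
|---|---|---|---|---|---|---|
| any | 0 | 1.00 | 6.9 | 5.5 | 200 | 95% |
| 5 (40) | 0.01 | 1.04 | 7.1 | 5.7 | 192 | 94.5% |
| 5 (40) | 0.05 | 1.20 | 7.6 | 6.1 | 167 | 92.6% |
| 10 (20) | 0.02 | 1.18 | 7.5 | 6.0 | 169 | 92.9% |
| 10 (20) | 0.05 | 1.45 | 8.3 | 6.7 | 138 | 89.6% |
| 10 (20) | 0.10 | 1.90 | 9.6 | 7.6 | 105 | 84.5% |
| 20 (10) | 0.05 | 1.95 | 9.7 | 7.7 | 103 | 84.0% |

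The last column applies only if the final analysis uses the unadjusted interval.

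**Step 3: separate the two effects.** At 10 women per midwife and ICC 0.02, the gap between the stated 6 points and 7.5 is 1.5 points. Of this, 0.9 is the arithmetic error in Step 1 and 0.6 is clustering.

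**Step 4: what a midwife-level ICC from this study could show.** With 20 midwives, 10 women each and a true ICC of 0.05, the large-sample standard error is √{2(1 − 0.05)² × 1.45² / [10 × 9 × 19]} = √(3.795/1710) ≈ 0.047. That is about as large as the ICC itself.

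**The case against.** The strongest reply is that clustering is not shown. The article gives no ICC and no number of midwives, and its sentence on provider influence says only that knowledge and attitude may affect the offer, and concerns GP practices. All antenatal providers are asked to take a common e-learning module, which may reduce differences between midwives. With about 40 midwives and an ICC of 0.01 to 0.05, the half-width moves only from 6.9 to 7.1–7.6 points, which matters little in a feasibility study. This stands as a limit on size. It does not remove the point, because the rationale section extends the expected influence of provider and setting to uptake as well as offer.

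Three stronger readings are tempting and are not supported.
- A reader might infer that the reported 95% intervals for both primary outcomes will undercover and that p-values will be too small. The article fixes the simple formula only for planning, and only for uptake. The CI method of the analysis is not named, the analysis plan is not shown, and no provider-level or site-level predictor is listed.
- A reader might infer that a hospital-level design effect is needed. If the target is uptake in these three hospitals, hospital is a fixed stratum. Midwife is the relevant layer.
- A reader might infer that the study fails its purpose by not planning to estimate the ICC that drives the future cluster trial. The article does not state that trial's unit of randomisation, three hospitals cannot give a usable hospital-level ICC, a midwife-level one would be imprecise (Step 4), and a condensed article may leave such a plan to the full protocol.

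**Conclusion.** The point holds conditionally. The Sample size calculation and the named association analyses assume independent women, in a design where the article's own reasoning expects provider and setting to matter. Under any positive within-midwife correlation the planned precision for uptake is optimistic. The offer proportion lies outside the calculation but would be affected in the same way if analysed by the same formula.

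The size cannot be fixed from the article. Over the assumed values tabulated, the half-width at 50% runs from 7.1 to 9.7 points against a correct independent value of 6.9. The lower end is negligible. At the upper end the effective sample is about half of the 200. The shortfall of the stated 6 and 5 points against 6.9 and 5.5 is certain and does not depend on clustering. This is an inexpensive improvement and does not invalidate the design.

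**What to change.** - Record an anonymised midwife code with each eligible booking, whether or not the test was offered or accepted.
- Compute the CIs for uptake and offer, and fit the logistic models, with midwife-clustered variance (GEE or cluster-robust, with a small-sample correction) and hospital as a fixed stratum. Report the three hospital-specific rates.
- In the Sample size section, restate the half-widths as 6.9 and 5.5 points, say that they assume no clustering, and add a sensitivity range such as the table above.
- A midwife-level ICC with its CI may be reported descriptively. It should not be presented as the parameter that determines the size of the future trial.

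The cost is one coded field, a different variance estimator and somewhat wider intervals. For bookings already made, the code would have to come from the antenatal records, if they hold it.
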